**Methods:**

One hundred twenty-eight cognitively healthy older adults will be recruited from the community in Switzerland, Canada and Belgium. The study will comprise (1) a 26-week double-blind randomized controlled efficacy trial and (2) a 22-week pragmatic adherence sub-study. In the efficacy trial, participants will be randomly assigned to an experimental or an active control intervention. In the experimental intervention, participants will use the StayFitLonger programme, which is computerised on a tablet and provides content that combines physical activities with a focus on strength and balance, as well as divided attention, problem solving and memory training. Outcomes will be measured before and after 26 weeks of training. The primary efficacy outcome will be performance on the “Timed-Up & Go” test. Secondary outcomes will include measures of frailty, cognition, mood, fear of falling, quality of life, and activities of daily living. Age, sex, education, baseline cognition, expectation, and adherence will be used as moderators of efficacy. Following the 26-week efficacy trial, all participants will use the experimental programme meaning that participants in the control group will ‘cross over’ to receive the StayFitLonger programme for 22 weeks. Adherence will be measured in both groups based on dose, volume and frequency of use. In addition, participants’ perception of the programme and its functionalities will be characterised through usability, acceptability and user experience.

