### Efficacy trial

#### Design

The design of the efficacy trial and adherence sub-study is illustrated in Table 1. The efficacy trial will be a double-blind parallel group multicentric RCT. It will be completed in three sites: Centre Leenaards de la mémoire – Centre hospitalier universitaire Vaudois (CHUV) in Switzerland; Institut universitaire de gériatrie de Montréal (IUGM) of the Centre intégré universitaire de santé et de services sociaux Centre-Sud-de-l’Île-de-Montréal (CIUSSS-CSMTL) in Canada; and Brusano and Centre Public d’Action Sociale (CPAS) of Woluwe-Saint-Lambert in Belgium. Participants will be randomised to one of two home-based computerised intervention conditions, the StayFitLonger training programme (experimental) or the comparator, an active control training programme. Outcome measures (Table 2) will be collected at two timepoints: pre-training (T0; within 6 weeks prior to the start of the intervention) and post-training (T1, within 4 weeks following the end of the 26-week training). Of note, a second exploratory post-training assessment (T2), not part of the RCT, will be performed within 4 weeks following the end of the adherence sub-study. At each timepoint, there will be two assessment visits. Within a month following the T0 assessment, introductory courses in groups of a maximum of six people will take place to introduce the features of the programme and describe the different physical and cognitive exercises. This will mark the beginning of the training that will take place at home for 26 weeks (see Table 1 for details). Participants will be supervised through home visits and monthly phone calls to monitor their use in relation to recommendation and address problems with the use of the programme.

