**Table 1 Tab1:**
[figure not shown]
Schedule of enrolment, assessments and interventions

**Table 2 Tab2:** List of outcomes measured for the RCT

RCT Outcomes				Timepoints		
***Domain***	***Primary outcome***			T0	T1	T2^a^
Physical	Mobility/gait	Timed-Up & Go (TUG) task		X	X	X
***Domain***	***Secondary outcomes***					
Physical	Mobility/balance	20-m Walking task		X	X	X
		Five Time Sit to Stand Test		X	X	X
		Four Stage Balance Test		X	X	X
		Gait Up sensor measurements: several walking parameters		X	X	X
Cognitive	Global cognition: ZAVEN Composite Score	Episodic memory composite	California Verbal Learning Test (CVLT): free delayed recall	X	X	X
			Wechsler Memory Scale (WMS-IV) Logical Memory Test: delayed recall	X	X	X
		Complex attention composite	Wechsler Adult Intelligence Scale (WAIS-IV) Digit Symbol Substitution Test (DSST)	X	X	X
		Executive function composite	Verbal Fluency task	X	X	X
	Memory Composite Score	CVLT: free delayed recall		X	X	X
		WMS-IV Logical Memory Test: delayed recall		X	X	X
	Executive and attentional functions Composite Score	Verbal Fluency test		X	X	X
		Trail Making Test: Part B- Part A		X	X	X
		Victoria Stroop Test (VST): high interference		X	X	X
		Test of Attention Performance (TAP): Divided Attention		X	X	X
	Speed processing Composite Score	Trail Making Test: Part A		X	X	X
		WAIS-IV DSST		X	X	X
		VST: “naming” condition		X	X	X
	Divided attention	Ad-hoc computerised multitasking task		X	X	X
	Prospective memory	Prospective memory items of the Rivermead Behavioural Memory Test (RBMT-3)		X	X	X
	Concept elaboration	Test of Attention Performance (TAP): Flexibility		X	X	X
		WAIS-IV Similarities		X	X	X
Affective	Mood	Hospital Anxiety and Depression Scale (HADS)		X	X	X
	Fear of falling	Falls Efficacy Scale International (FES-I)		X	X	X
Psycho-social	Quality of Life	The Older People Quality of Life questionnaire (OPQOL 35)		X	X	X
	Subjective difficulties encountered in activities of daily living	Cognitive Function Instrument (CFI)		X	X	X
		Everyday Cognition (E-Cog)		X	X	X
	Expectation questionnaire	Ad-hoc questionnaire on participant’s expectation on the programme		X	X	X

^a^T2 assessment is listed here but it is not technically part of the RCT

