
*Affective domain*. Mood will be assessed using the Hospital Anxiety and Depression Scale (HADS) [72]. Fear of falling will be measured with the Falls Efficacy Scale-International (FES-I) [73].

*Psychosocial domain.* Quality of life will be assessed with the 35-item Older People Quality of Life questionnaire (OPQOL 35) [74]. Cognition in everyday life will be measured with the self-reported Cognitive Function Instrument (CFI) [75] and Everyday Cognition scale (E-Cog) [76]. The CFI will include 14 questions to measure subjective concerns regarding cognition and activities of daily living over the last year. The E-Cog will measure how cognitive functions in different domains (everyday memory, language, visuospatial abilities, planning, organisation, divided attention) impact activities of daily living compared to 10 years ago. Participant’s expectation toward the efficacy of the training programme will be assessed with an ad-hoc 17-item questionnaire.

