#### Variables

*Adherence.* For the entire duration of the study (between T0 and T1, and T1 and T2), three measures of adherence in relation to the device usage will be recorded directly from the application (Table 3): dose measured by the time (min) spent on the programme per week; volume corresponding to the total number of repetitions performed per week within each activity (e.g., 3 quizzes completed while using the Quiz activity); and frequency corresponding to the number of sessions per week. These will be recorded separately for the physical and cognitive activities. Adherence will be calculated for each individual by plotting weekly data over the entire training period.

**Table 3 Tab3:** List of variables measured during the adherence sub-study

Adherence sub-study variables		Timepoints		
***Domain***	***Variable***	T0	T1	T2
Adherence	Dose variable: total time of training for each activity	During training		
	Volume variable: number of times each activity is carried out			
	Frequency variable: number of training sessions of at least 30 min performed per month			
User experience	Ad-hoc questionnaire exploring the quality of the introductory course	X		
	AttrakDiff 2 scale		X	X
Acceptability	Ad-hoc questionnaire to obtain ratings on different components (enjoyment, appropriateness, safety, self-evaluation)		X	X
Usability	Ad-hoc questionnaire exploring the impact of unique features of the programme (virtual coach, social interactions, preference, gamification, educative content, self-management, usability)			X

*User experience.* The AttrakDiff 2 scale [78] will evaluate user experience (Table 3) with a 28-item questionnaire given at T1 and T2. It will measure attractiveness, pragmatic quality and hedonic qualities (stimulation and identity) of the application. Pragmatic quality corresponds to usability for instance efficiency, effectiveness and learnability. Hedonic qualities refer to the programme’s originality and beauty. In addition, a 9-item questionnaire will be given at T0 to ask participants’ knowledge regarding the effects of cognitive and physical interventions and the quality of the introductory courses.

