The StayFitLonger study will provide critical information on usability, acceptability and user experience, which are inter-related concepts providing insights on the potential long-term use of a technology [36, 37]. Usability refers to the ease of use of a technology and is characterized as a person’s perception of its efficacy, efficiency and satisfaction [82]. Acceptability is an a priori willingness to use a tool, while acceptance is an a posteriori pragmatic evaluation of a tool after its use [83]. They are known to be influenced by usability but also by other factors, such as perceived usefulness by the user and others, and this is particularly true among seniors [82]. User experience, which refers to a person’s perceptions and responses that result from the technology use and/or anticipated use is also dependant on usability and has an impact on acceptability [84]. Results obtained on these parameters are important to determine the factors that influence future use, but they can also help improving the application or designing new solutions to provide the best experience for end users.

The design includes an active control training as a comparator that mirrors the structure of the StayFitLonger training. Using an active control condition will allow us to attribute the improvement to the particular content and format of the StayFitLonger programme. Relying on an active control condition as a comparator is a methodological strength compared to other studies that used a no-contact or wait-list control condition. However, this comes with additional challenges in terms of design and power. One of these challenges is that we need to ensure that participants in each group have the same expectation regarding the capacity of their assigned training to yield improvement [48]. To control for this effect, we included an expectation scale and will assess whether it differs among groups and whether expectations are related to pre-post changes.

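### The expectation questionnaire has no stated measurement between introduction to the assigned programme and the end of training, so it cannot establish that the two arms expected equal benefit

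*Protocol article*

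**What the plan says.** In the Discussion, the authors write that with an active control they must ensure that "participants in each group have the same expectation regarding the capacity of their assigned training to yield improvement". Their answer is that "we included an expectation scale and will assess whether it differs among groups and whether expectations are related to pre-post changes". The Secondary outcomes section describes the instrument but gives no time for it: "Participant’s expectation toward the efficacy of the training programme will be assessed with an ad-hoc 17-item questionnaire".

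Table 2 lists "Ad-hoc questionnaire on participant’s expectation on the programme" with marks at T0, T1 and T2, and its footnote places T2 outside the RCT.

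The Design section of the efficacy trial defines T0 as pre-training, within 6 weeks before the intervention starts. It then states: "Within a month following the T0 assessment, introductory courses in groups of a maximum of six people will take place". T1 falls within 4 weeks after the 26 weeks of training end.

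Two other places bear on the point. In the adherence sub-study (Variables, and Table 3), "a 9-item questionnaire will be given at T0", and part of its content is the quality of the introductory courses. The abstract says "Age, sex, education, baseline cognition, expectation, and adherence will be used as moderators of efficacy", whereas Analysis of moderators names only age, sex, education and MoCA score, which it treats as time-invariant.

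**The concern.** The control application has fewer exercises and lacks interactive exercise content, personalisation, coach rewards, chat and psychoeducation (Active control training programme). A participant who meets one application or the other may form a different view of how much it will help. If the StayFitLonger arm then does better on the TUG or the secondary outcomes, different expectations are a plausible rival explanation, and the Discussion acknowledges this.

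A check on that explanation needs a score taken once participants know their programme and before they have felt any result. If no such score exists, a finding of equal expectations could be reported as reassurance that it does not give. A correlation between expectation and change could likewise be read as evidence for or against expectancy when it supports neither.

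**Working it through.** No figure in the plan is at issue, so the check sets the stated sequence beside what the scale has to show.

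| Point | Place in the sequence | What an arm difference in expectation can mean |
|---|---|---|
| T0 | Pre-training, before the courses (Design) | Chance; the assigned programme has not been introduced |
| Introductory courses | Within a month after the T0 assessment (Design) | Expectation about the assigned programme; no measurement listed |
| T1 | After 26 weeks of use (Design) | Expectation and perceived benefit together |
| T2 | After the sub-study, outside the RCT (Table 2 footnote); in Switzerland and Canada, after the control arm has crossed over (Adherence sub-study, Design) | Not a comparison of the two assigned programmes at those sites |

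**Arm comparison.** Let d be the arm difference in expectation created by meeting the assigned programme. Let b be the arm difference at T1 that comes from perceived benefit.
- At T0 the expected arm difference is 0 by randomisation, whatever the value of d. Equality at T0 therefore says nothing about d.
- At T1 the arm difference is d + b: one observed quantity and two unknowns. A positive difference fits d = 0 with b > 0 (the programme helped and people noticed) as well as d > 0 with b = 0 (expectation only). A difference of 0 fits d = 0 with b = 0, and also d > 0 with b = −d (high hopes followed by disappointment).

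**Relation to pre-post change.** If people who improved report higher expectation at T1, that score correlates with change even when expectation caused none of it. The T0 score does not have this problem, because it precedes training. It can legitimately predict change or be tested as a baseline moderator, but it measures expectation before the assigned programme is known.

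**Meaning of T0.** The form on course quality carries the T0 label, yet the courses follow the T0 assessment. Either that form is mislabelled or T0 covers more than the pre-training visit. No section says that the expectation form is given after the courses.

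**Moderators.** Adherence arises after randomisation, so it is not a baseline moderator of the randomised effect. It is also recorded unequally: the stop after 10 minutes of inactivity exists only in the StayFitLonger application (Discussion). The Statistical analyses section of the sub-study already treats it suitably, as a correlation with change scores.

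**Reach of a remedy.** The planned sample is 64 in Switzerland, 32 in Canada and 32 in Belgium (Study population). Recruitment was complete in the first two (Trial status): 64 + 32 = 96, and 96/128 = 75%. Belgium is 32/128 = 25%, and its recruitment had begun in January 2020, so some of those participants may also be past their courses.

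**The case against.** The strongest reply is that the T0 label is elastic. One form labelled T0 can only be completed once the courses have been held, so the expectation form may be handled the same way. Table 1, the schedule that could settle this, is not reproduced in the text at hand, and the time of randomisation relative to T0 is not stated. This doubt stands, and it is why the first step is to reconcile the sections. It does not remove the problem. The Design section defines outcome collection at T0 as pre-training, and no section places the expectation form later. Even if allocation came before T0, the first described contact with the application is still the courses.

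A second reply is that the plan has other protections. Participants are not told the hypotheses, both applications have a similar main screen and name, and the recruitment and consent wording is neutral. The same instructors present both programmes in similar ways, and assessors are blinded. A reader might infer that the scale is the only safeguard; the documents do not support that. These measures lower the risk of unequal expectations, but they do not show that expectations were equal, which is what the scale is meant to do.

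A third reply is that a moderator list in an abstract may simply condense several sections. That is fair, and the mismatch with Analysis of moderators is mainly loose wording. The abstract does not name T1 expectation as a moderator, so that reading should not be put on it.

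**Conclusion.** The point holds as a limit on interpretation. Followed as written, the plan has no expectation score taken after introduction to the assigned programme and before training effects. The arm comparison cannot establish equal expectations, and a T1 correlation with change cannot separate expectancy from true effect.

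A reader might go further and infer that the scale can never show an arm difference, or that T0 scores are worthless. Neither follows. T1 can show a difference, though not whether it preceded training or reflects felt benefit. T0 remains a valid baseline predictor of change.

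The size of any expectancy bias cannot be calculated from the documents. The TUG estimate and the power are not altered; what is weakened is the attribution of a positive result to programme content. The conclusion assumes that the order in the Design section applies to the expectation form. If the form is in fact given after the courses and before home training, stating so would resolve most of the point.

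**What to change.** 1. Reconcile the use of T0 in the Design section, Table 2 and the sub-study's Variables section and Table 3, and state when the expectation form and the course-quality form are given.
2. Where courses are still to come, give the 17-item form at the end of the last introductory session. Use that score for the arm comparison. Do not put it in the primary model as an adjustment covariate: it is measured after randomisation and may be affected by arm, so adjusting for it could remove part of the treatment effect or bias it.
3. For participants already past the courses without such a score, report T1 expectation descriptively and state that expectancy cannot be ruled out. Keep T0 expectation as a baseline predictor.
4. Align the abstract with Analysis of moderators: describe adherence as an exploratory association arising after randomisation, as the sub-study analysis does, rather than as a moderator.

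The cost is one extra short questionnaire in a session already planned. The main drawback is reach. At the stated trial status the added score is available only for the remaining Belgian participants, a small subset from one country, so for most of the sample the remedy is the limited conclusion in step 3.

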#### Statistical analyses

Dose, frequency and volume variables will be analysed with polynomial regression models including linear and non-linear trajectories. This will allow to establish the best fitting model describing the use of the programme over time. Regression analyses will examine whether the cumulative values on adherence variables are predicted by personal characteristics, and the group to which they were assigned. We will also examine adherence dichotomously by classifying participants as a function of whether they maintain or not the recommended dose of the programme over time. Finally, we will evaluate whether change scores on primary and secondary measures of efficacy are correlated with adherence.

Qualitative analyses will be used to characterize usability, acceptability and user experience. In addition, correlations analyses between these parameters and a series of variables (age, sex, education, cognitive profile, participant’s technology and gaming profile) will be performed.

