We are aware of the potential limitations associated with this study. First, the StayFitLonger study spans over a full year and it is hard to predict whether participants will commit for such an extended period of time. Note, however, that we rely on a two-part design, with the RCT portion only lasting 26 weeks, and that attrition will be examined separately for the two portions. Second, while the use of feedback and rewards in the programme was meant to boost motivation, the frequency at which they appear has been set as a fixed parameter to avoid a bias between participants. Hence, this aspect was not personalized. In order to take into account that some participants may dislike receiving regular feedback, they will be able to deactivate this feature during the adherence sub-study. Adherence will be measured from the tablet application, but it is possible that some participants, intentionally or not, start an activity and let the application run in the background while they are actually not doing the activity. To counteract this possibility, the StayFitLonger programme includes a function that stops the application after 10 min of inactivity. However, it has not been implemented in the active control programme. This will be monitored as carefully as possible during data analysis to assess possible outliers in the time of use data of the active control group.

In conclusion, the StayFitLonger study will examine the efficacy, adherence and perception of a home-based computerised multi-modal training programme in robust and pre-frail older adults. Positive results on the StayFitLonger study will pave the way to further development and commercialisation of a scientifically grounded and empirically validated application which will improve the physical and cognitive health associated with independent life at home.

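### Logged minutes of use can be inflated in the control arm during the 26-week RCT, because only the StayFitLonger app stops when idle, and a control-only outlier check does not correct this

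*Protocol article*

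**What the plan says.** Under Adherence sub-study, Variables, dose is "dose measured by the time (min) spent on the programme per week", recorded by the application itself. Volume counts repetitions. Frequency is sessions per week in the text, but Table 3 counts only sessions of 30 min or more, per month.

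The limitations paragraph of the Discussion accepts that "it is possible that some participants, intentionally or not, start an activity and let the application run in the background". As a safeguard, the StayFitLonger app has a function that "stops the application after 10 min of inactivity. However, it has not been implemented in the active control programme". The handling offered is careful monitoring at analysis to "assess possible outliers in the time of use data of the active control group".

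Under Adherence sub-study, Statistical analyses, regressions will test whether cumulative adherence is "predicted by personal characteristics, and the group to which they were assigned". Participants will also be classified by whether they keep to the recommended dose, and change scores will be correlated with adherence. Objectives and hypotheses lists the type of intervention among the influences on adherence to be examined. After week 26 the control group moves to the StayFitLonger app for 22 weeks.

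**The concern.** In weeks 1-26 one variable, minutes of use, is recorded under a different rule in each arm. If participants leave the app open, the experimental record stops after 10 idle minutes while the control record keeps running. This measurement error depends on assigned group, and group is a predictor in the planned regression.

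The error can only raise control minutes relative to experimental minutes. The Discussion expects the virtual coach to increase adherence in the experimental programme, so the artefact works against the difference the sub-study hopes to see and could hide it. It could also make control participants' use appear to fall when they cross over to the app with the cut-off.

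The stated remedy does not match the problem. An outlier check looks for extreme values, whereas moderate idle time can pass as ordinary use. Applying it to one arm only adds a second difference in how the arms are handled.

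**Working it through.** The plan gives no figure for idle time or its effect, so there is nothing to reproduce. The sizes below are illustrations.

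**Inputs from the protocol article**
- Idle cut-off: 10 min in StayFitLonger, none in the control app (Discussion).
- Recommended use (Introductory courses): physical exercise 30 to 45 min over the day, three sessions a week; cognitive exercise at least 3 times a week for 15 min.
- Periods: 26 weeks on different apps, then 22 weeks on the same app, 48 in all.

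**Assumptions**
- One idle episode per week, of length L = 30, 60 or 120 min. The document gives neither rate nor length.
- The experimental app records the idle minutes up to the cut-off. If it discards them when it stops, each excess below is 10 min larger.
- The 30 to 45 min of exercise applies to each of three training days.

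**Recommended weekly minutes**
- Low: 3 × 30 + 3 × 15 = 135.
- High: 3 × 45 + 3 × 15 = 180.
- Cognitive part alone: 3 × 15 = 45.

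**Excess per episode**

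Control records L and experimental records min(L, 10), so the difference is max(0, L − 10). It is zero for L of 10 min or less and never negative.

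| L (min) | Excess (min/week) | % of 180 to % of 135 | % of 45 |
|---|---|---|---|
| 30 | 20 | 11 to 15 | 44 |
| 60 | 50 | 28 to 37 | 111 |
| 120 | 110 | 61 to 81 | 244 |

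The last column applies only if all the idle time falls in cognitive activities.

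**Cumulative dose over 48 weeks, L = 60**
- Excess: 50 × 26 = 1300 min. Weeks 27-48 add nothing.
- Relative to the recommended total: 1300 / (135 × 48) = 20%; 1300 / (180 × 48) = 15%.

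**Table 3 frequency**

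Take a 15-min cognitive session followed by idle time. StayFitLonger logs at most 15 + 10 = 25 min, so it never reaches the 30-min threshold. The control app reaches it once idle time is 15 min. Idle time alone can thus create qualifying sessions in the control arm.

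**Would an outlier check catch it?**

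Fifteen minutes of control exercise followed by 30 idle minutes logs as 45 min, the top of the recommended daily exercise time. Nothing about it looks extreme.

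**Effect of a common rule**

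With the same cut-off applied to both arms' logs, each arm records min(L, 10), and the difference per episode is zero.

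**The case against.** The authors disclose the gap and say they will look for it. An article may leave a detailed cleaning rule to a fuller document, so the absence of a threshold is not itself a fault. That stands. The approach the article does choose is still open to criticism: outlier screening in one arm cannot equalise two recording rules.

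The article does not say whether outliers are judged by session or by week. A 60-min entry against a recommended 15-min cognitive session might well be flagged. This is fair, and it limits the criticism to moderate idle time, as in the 45-min example.

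A single 10-min truncation is not obviously neutral either. The control exercises have no videos or other interactive content (Active control training programme), so a participant may exercise for longer than 10 min without touching the screen. Truncation could then delete genuine use and reverse the bias. This stands and shapes the fix.

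The before/after contrast in controls is also confounded by the change of programme, so idle time is only one of its problems. The article does not say whether the correlations with change scores pool the arms; they are exposed to this between-arm error only if they do.

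A reader might infer that every between-arm dose comparison is biased. The documents do not support that: from week 27 both groups use the app with the cut-off. A reader might also take inflation as established, but the Discussion calls idle running only possible and gives no rate.

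**Conclusion.** The concern holds in a limited form. During the 26-week RCT, control minutes can be inflated relative to experimental minutes, and the error cannot run the other way. It can affect between-arm dose in weeks 1-26, 48-week cumulative dose by group, classification against the recommended dose, the control cross-over contrast and Table 3 frequency.

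Comparisons confined to weeks 27-48 and volume counts are free of this artefact. The primary Timed-Up & Go comparison uses no logged minutes, so the finding should not be read as a threat to the efficacy result.

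The size is unknown. Under the assumed one episode a week, it ranges from 11-15% to 61-81% of the combined recommendation for idle periods of 30 to 120 min, and is nil for periods of 10 min or less. The 44%, 111% and 244% figures should not be quoted as the general effect, since they assume that all the idle time falls in the 45-min cognitive component. This deserves correction before adherence is analysed, as a matter for the sub-study.

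**What to change.** Replace the control-only outlier check with one inactivity-truncation rule, specified before the adherence analysis and applied identically to both arms' event logs. Report between-arm dose with and without truncation, because control exercises may produce long spells without screen events.

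If the control logs lack event times, remove minutes and any frequency measure with a duration threshold from every comparison that involves control-app weeks. Use sessions per week without a duration threshold there, as the text of Variables defines frequency, with volume as support. The text and Table 3 definitions of frequency should be reconciled at the same time.

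The cost is a data-processing script and a short addition to the plan, with no change to the apps or to participants' burden. The real downside is that, if the logs are too coarse, dose is lost as a between-arm measure for weeks 1-26.
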